### Objective

The primary objective of this study is to compare, using a crossover design, the analgesic efficacy of intravenous ketamine with that of placebo in patients with intractable NP. Secondary objectives are as follows:To compare the additive analgesic efficacy of magnesium and ketamineTo study the time course of pain and analgesia after intravenous administration of ketamine, ketamine-magnesium, and placebo

### Eligibility

#### Inclusion criteria

Patients ≥ 18 years oldPatients with chronic pain (for > 3 months), having the characteristics of a peripheral or central neuropathy justifying implementation of a therapeutic program with courses of intravenous ketamine injectionPatients who have never received ketamine infusion for care of their NPHistory of illness compatible with an injury or disease of the somatosensory systemLocalized pain in a neuroanatomical territoryNeurological examination shows sensory abnormalitiesFor women of childbearing age, they will be enrolled in the study after a negative urine pregnancy test; in case of suspicion of pregnancy, a blood pregnancy test should be performed.Cooperation and willingness to follow the studyAcceptance to give written consentAffiliated with the French social security systemInscription or acceptance of inscription in the national register of volunteers involved in trials

#### Exclusion criteria

Patients who have received an intravenous ketamine infusionPatients with one or many contraindications to ketamine administration: known hypersensitivity to ketamine in which one of the constituents of the product, uncontrolled high blood pressure, severe cardiac insufficiencyPatients with one or many contraindications to magnesium sulfate administration: patients with severe renal impairmentPatients with one or many contraindications to administration of sodium chloride: water inflation, fluid retentionPatients with a medical history and/or surgical history judged by the investigator not to be consistent with the clinical trialPatients with drug treatments judged by the investigator not to be consistent with the clinical trialPregnant or lactating womenPatient who participated in another clinical trial, located in the exclusion period, or received benefits > €4500 during 12 months before the beginning of the trialPatients with cooperation and understanding not strictly adherent to the conditions of the clinical trial Patients receiving a measure of legal protection Patients not affiliated with the French social security system

### Definition of outcome measures

#### Outcome measures

The primary outcome is the AUC of pain intensity assessed on a 0–10 NPRS for a period of 5 weeks (35 days) from the day of intravenous treatment.

#### Secondary outcome measure

Secondary endpoints are the evaluation of pain (NPRS, NPSI, BPI, McGill Pain Questionnaire, PGIC), anxiety and depression (HADS), quality of life (SF-36), and quality of sleep (PSQI) using a variety of scales and questionnaires. Furthermore, the intensity of the average and maximum pain scores as well as concomitant analgesic treatments will be reported in a daily pain diary. The various assessments and questionnaires are summarized in Fig. 2.

**Fig. 2 Fig2:**
[figure not shown]
Summary of assessments

### Recruitment

This clinical trial will be carried out by the physicians of the pain clinic and of the clinical pharmacology center/CIC Inserm 1405 of CHU Clermont-Ferrand in charge of the project. The number of subjects needed (*n* = 22) is quite realistic according to the recruitment capacities of the pain clinic. The duration of recruitment is expected to be 2 years.

### Allocation concealment

On the day of the first visit, inclusion and exclusion criteria are verified, and written informed consent is obtained by the physician. A clinical nurse independent from the protocol obtains the randomization number from the hospital pharmacy, and the patient is then randomized into one of the three groups. The assignment to the treatments will follow a predetermined randomization list and is generated using random blocks by a clinical research associate totally independent from the protocol. The randomization list and a copy will be edited, placed in a sealed envelope, and handed over to the Clermont-Ferrand University Hospital Pharmacy and to the coordinating center, the Clinical Research Center of Clermont-Ferrand University Hospital.

### Blinding

In order to maintain blinding, packaging will be identical. The clinical research center and the pain clinic are situated on the same floor of the Clermont-Ferrand University Hospital. A clinical nurse of the clinical research center independent from the protocol prepares and gives the treatment to the patient in a room in the pain clinic. The persons who administer and provide clinical supervision are the medical team affiliated with the pain clinic of the University Hospital of Clermont-Ferrand. The person who performs all questionnaires and analyses is not involved in other aspects of the protocol. Furthermore, only ketamine-naïve patients are included in this trial in order to avoid detection of the placebo or the active substance, taking into account the dysphoric effects (even minor) that may accompany ketamine infusion. If an adverse event occurs (e.g., hospitalization or prolonged hospitalization, incapacity or disability), treatment of the enrolled patients will immediately be suspended. The drug dose will not be changed, and treatment will be continued only upon agreement of the sponsor and the investigators if they conclude that the cause of the adverse event is not related or unlikely to be related to the study products. Unblinding will be allowed only in case of a serious adverse event. Only a doctor involved in the protocol but not in the administration or evaluation of the drug will be dealing with such events. All these steps will be conducted and documented according to the procedures of the University Hospital of Clermont-Ferrand and the current regulatory requirements. If an adverse event persists at the end of the study, the investigator will follow the patient until the event is resolved.

### Missing data

Concerning missing data, if the participant misses one of the three treatment blocks, the patient will be excluded from the study. If missing data occur, a sensitivity analysis will be proposed in order to define the level of attrition and the statistical nature of the missing data, and the last data obtained will be reported.

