**Methods/design:**

A randomized, double-blind, crossover, placebo-controlled study will be performed in Clermont-Ferrand University Hospital, Clermont-Ferrand, France. The aim is to evaluate the effect of ketamine with or without magnesium in 22 patients with neuropathic pain. Intravenous ketamine/placebo, ketamine/magnesium sulfate, or placebo/placebo will be administered consecutively to each patient, in random order, once at 5-week intervals. The primary endpoint is the AUC of pain intensity assessed on a 0–10 Numeric Pain Rating Scale for a 5-week period. Data analysis will be performed on an intention-to-treat basis, and all statistical tests (except primary analysis) will be performed with an α risk of 5% (two-sided).

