### Sample size calculation

To highlight the analgesic efficacy of intravenous ketamine in patients with intractable NP, sample size estimation was based on a pilot study done at the pain clinic of the University Hospital of Clermont-Ferrand (administration of intravenous ketamine in a similar open-label population), showing an AUC (28 days) of the intensity of pain of 164 ± 38 (unpublished data). Furthermore, in a study comparing similar treatments (ketamine and placebo) in a different chronic pain setting (CRPS), the AUC graph estimate suggested a 35% reduction in AUC (at 28 days), that 18 patients are needed to detect a minimum difference of 57 in the primary outcome, with a two-sided type I error of 1.67% (to take account of multiple comparisons), statistical power of 90%, and an intraindividual correlation coefficient of 0.5 (owing to the crossover design and no carryover effect assumed) [46]. Considering data from our center, a recent study [46] (NCT01602185) currently submitted to a peer-reviewed journal but not yet published clearly shows that pain evaluation remains the same from 28 days to 60 days. Ultimately, allowing for patient dropout for adverse events or premature withdrawal, we plan to recruit 22 subjects.

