### Statistical analysis

Statistical analysis will be performed on an intention-to-treat basis using Stata software (version 13; StataCorp, College Station, TX, USA) for a two-sided type I error at α = 5%. Continuous data will be described as mean ± SD or median (IQR) according to the statistical distribution (assumption of normality studied by Shapiro-Wilk test). Categorical parameters will be described as number and percent. The primary endpoint (AUC of pain intensity based on NPRS) will be compared between groups by repeated measures analysis of variance (ANOVA) for crossover designs, taking account of the following effects: treatment group (ketamine versus placebo), sequence, subject (as random effect), and carryover. Then, the “sequence × treatment” interaction will be tested; if it is significant, statistical analysis will cover only the first period of the crossover study. The normality of residuals will be studied. When quantitative endpoints do not meet the normality assumption, a nonparametric paired Wilcoxon test will be used. Sensitivity analysis will determine the statistical nature of missing data to apply the most appropriate imputation approach.

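### Excluding any patient who misses one of the three treatment blocks conflicts with the stated intention-to-treat analysis

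*Protocol article*

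**What the plan says.** The Missing data section states that "if the participant misses one of the three treatment blocks, the patient will be excluded from the study". It then adds that "a sensitivity analysis will be proposed in order to define the level of attrition and the statistical nature of the missing data" and that the last available data will be reported.

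The abstract states that "Data analysis will be performed on an intention-to-treat basis", and the Statistical analysis section that "Statistical analysis will be performed on an intention-to-treat basis using Stata software". The primary model there is a crossover analysis of variance whose effects, besides treatment, are "sequence, subject (as random effect), and carryover". If the sequence-by-treatment interaction is significant, only the first period is analysed. The same section says that "Sensitivity analysis will determine the statistical nature of missing data to apply the most appropriate imputation approach".

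The Sample size calculation arrives at 18 patients and, "allowing for patient dropout for adverse events or premature withdrawal, we plan to recruit 22 subjects". The Blinding section suspends treatment after certain adverse events. It allows treatment to resume only if the sponsor and investigators judge the event unrelated, or unlikely to be related, to the study products.

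**The concern.** Intention to treat keeps randomised patients in the analysis whatever happens afterwards. The exclusion rule removes them because of an event after randomisation. As written, two statisticians could build different primary analysis sets from this text, and each could cite it.

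Three things are at stake.

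- **Selection.** A block can be missed because of the treatment received, so those removed may differ systematically from those kept.
- **First-period fallback.** There the comparison is between patients. Removing someone with a complete first period because of a later missed block makes the compared groups depend on what happened after randomisation.
- **Discarded data.** Completed periods would be lost from a 22-patient trial. The primary objective compares ketamine with placebo, yet a patient who misses only the ketamine-magnesium block, and so has both periods needed, would also be excluded.

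**Working it through.** **1. The statements side by side.** The exclusion rule stands in the section on handling missing data, and its trigger is a missed block. Intention to treat is stated twice. The sentences on attrition, last data and imputation do not say that a patient with a missed block remains in the primary analysis; they could equally concern incomplete diaries in patients who had all three infusions. The random subject effect can use patients with one or two observed periods, so the model does not require the exclusion.

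**2. Link to treatment.** Under the Blinding section, an adverse event judged related to the study products prevents resumption and so leads to a missed block; the Missing data section then excludes the patient. The Sample size calculation expects dropout both for adverse events and for premature withdrawal. Exclusion may therefore depend on treatment. The document does not say how often.

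**3. Data discarded.** Inputs: 22 recruited, 18 needed.
- Implied allowance: 22 − 18 = 4 patients, 4/22 = 18.2% (the document states no rate).
- Suppose each of the 4 misses exactly one block. Completed periods = 18 × 3 + 4 × 2 = 62, of 22 × 3 = 66 planned.
- Discarded under the rule: 8/62 = 12.9%.

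**4. Power.** Inputs from the Sample size calculation: SD 38, difference 57, two-sided α 1.67%, power 90%, within-patient correlation 0.5.
- SD of a paired difference = 38 × √(2 × (1 − 0.5)) = 38.
- Normal approximation: n = (38 × (2.393 + 1.282)/57)² = 6.0. The exact paired t calculation gives 10.
- The stated 18 is not reproduced. That is a separate matter, and this point does not rely on it.
- Power at 18 completers exceeds 99%, and 90% is kept down to 10.
- The expected number of completers for an assumed miss rate q per infusion is:

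| q | periods 2–3 can be missed: 22(1−q)² | any period can be missed: 22(1−q)³ |
|---|---|---|
| 5% | 19.9 | 18.9 |
| 10% | 17.8 | 16.0 |
| 15% | 15.9 | 13.5 |

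All of these stay above 10.

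**5. Bias in the within-patient comparison.** A simulation used 4,000 replicates, 22 patients, six sequences, SD 38, correlation 0.5 and a true ketamine-placebo difference of −57. The dropout mechanisms are assumptions.

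| Dropout after periods 1 and 2 | All observed periods | Completers only |
|---|---|---|
| 10%, at random | −57.0 (SE 8.66) | −57.0 (SE 9.11) |
| 15% after active, 2% after placebo, unrelated to pain | −57.2 (SE 8.75) | −57.2 (SE 9.13) |
| 35% if the period's AUC exceeded 190, otherwise 3% | −57.0 (SE 8.44) | −55.6 (SE 8.64) |

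Under random dropout the variance rises by (9.11/8.66)² − 1 = 11%. Under pain-driven dropout, completers-only estimation is off by 1.4 units, here towards a smaller benefit.

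**6. First-period fallback.** 22/3 gives about 7 patients per arm. Removing those who later miss a block takes patients out of each arm at a rate that may depend on the first treatment. Bias follows if those removed also differ in pain. No within-patient contrast cushions this.

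**The case against.** The strongest defence is that exclusion from the study may mean only that participation ends, with data already collected still analysed. The sentences on attrition, last data and imputation, and the random subject effect, fit that reading, and an article may leave the exact analysis set to the full protocol or SAP. The reading is possible. It is not the plain one: the rule stands under missing-data handling and nothing says the completed periods are kept. The point is also not a missing detail, because a stated rule conflicts with a stated analysis set.

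Three stronger readings are tempting, and the objection to each stands.

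- **Dropout is caused by treatment.** The Sample size calculation also names premature withdrawal and attributes no loss to treatment. The Blinding section foresees events unrelated to the study products, and patients can also leave after placebo.
- **The completers' result overstates the effect by 22%.** This comes from 57 × 18/22 = 46.6 and 57/46.6 = 1.22. It needs all four losses to occur, all four to have zero benefit, and completers to have the full 57, which the plan gives as the difference to detect. The simulations did not test zero benefit among dropouts, so they do not rule this out. The bias they did show was small and in the other direction. The mixed model alone would not recover 46.6, since it cannot supply a contrast a patient never provided.
- **Power is at risk.** On the plan's own inputs it is not.

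**Conclusion.** The point holds as a conflict between two stated rules. On its plain reading, the missing-data rule restricts the analysis to three-period completers, which is not intention to treat. A reader might infer that the trial is already fixed as a completers' analysis; the text does not settle that, because the milder reading remains open.

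The document does not establish the size or direction of bias in the within-patient analysis. The exposure is clearest in the first-period fallback, where exclusions linked to treatment and pain would bias a between-patient comparison. The measurable loss is up to 8 of 62 completed periods (13%), assuming four losses with two completed periods each. The harm is to validity and consistency, and the analysis set should be settled before unblinding.

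**What to change.** Replace the exclusion sentence with a rule on these lines: a missed treatment block is treated as missing data; all observed periods of every randomised patient enter the primary random-subject crossover model by assigned sequence; all randomised patients with period 1 data enter any first-period analysis; and the analysis of patients with all three periods is reported only as a sensitivity analysis. The Missing data section, the Statistical analysis section and the abstract would then agree.

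This concerns data retention and analysis only. It does not alter who receives further infusions. The cost is a wording change and minor programming, with no change to the number recruited.

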### Data handling and record keeping

We have not established a data and safety monitoring board for this study. However, in order to improve adherence to the intervention, the case report forms will be monitored by a clinical research associate independent from the protocol and will address any safety or other concerns that may arise. During these visits, the following elements will be reviewed: informed consent; compliance with the study protocol and the procedures defined; and quality of data collected in the case report form, including accuracy, missing data, consistency of data with source documents (e.g., medical records, appointment sheets, laboratory results), and management of the pharmaceutical drugs. Then the monitored case report forms will be retained at the data management center (CIC-Inserm 1405, Clermont-Ferrand, France) in a secure, locked room. Then data will be entered by double data entry by two people independent from the protocol. The blocked database will be transferred to the statistician responsible for the statistical analysis. All original records (consent forms, case report forms, questionnaires, and pain diaries) will be kept at the trial site for 15 years. All data will be anonymized and identified by a participant code.

### Sample size calculation

To highlight the analgesic efficacy of intravenous ketamine in patients with intractable NP, sample size estimation was based on a pilot study done at the pain clinic of the University Hospital of Clermont-Ferrand (administration of intravenous ketamine in a similar open-label population), showing an AUC (28 days) of the intensity of pain of 164 ± 38 (unpublished data). Furthermore, in a study comparing similar treatments (ketamine and placebo) in a different chronic pain setting (CRPS), the AUC graph estimate suggested a 35% reduction in AUC (at 28 days), that 18 patients are needed to detect a minimum difference of 57 in the primary outcome, with a two-sided type I error of 1.67% (to take account of multiple comparisons), statistical power of 90%, and an intraindividual correlation coefficient of 0.5 (owing to the crossover design and no carryover effect assumed) [46]. Considering data from our center, a recent study [46] (NCT01602185) currently submitted to a peer-reviewed journal but not yet published clearly shows that pain evaluation remains the same from 28 days to 60 days. Ultimately, allowing for patient dropout for adverse events or premature withdrawal, we plan to recruit 22 subjects.

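### The 18 patients said to be needed for a difference of 57 cannot be reproduced for this crossover: the stated inputs need about 8 to 10, so the formula or an input is wrong or unstated

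*Protocol article*

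**What the plan says.** All the inputs are in the protocol article, Sample size calculation. The pilot study is reported as "showing an AUC (28 days) of the intensity of pain of 164 ± 38". The effect comes from a study in another chronic pain setting, where "the AUC graph estimate suggested a 35% reduction in AUC (at 28 days"). The text then says that "18 patients are needed to detect a minimum difference of 57 in the primary outcome". The alpha behind this number is given as "two-sided type I error of 1.67% (to take account of multiple comparisons"), the power is 90%, and the assumed correlation between periods is "an intraindividual correlation coefficient of 0.5 (owing to the crossover design and no carryover effect assumed"). The 18 are raised to 22 for dropout, with no rate given. No formula or software is named for the sample size.

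Under Regimen, every patient receives all three products. Under Statistical analysis, the primary endpoint is compared by a crossover ANOVA with subject as a random effect. The comparison is therefore within patients.

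**The concern.** This paragraph is the only justification of the trial's size. A reader who puts its inputs into a within-patient calculation gets roughly half of 18. An unsuitable formula would mean that the paragraph describes a different design from the one being run. A misreported SD or correlation would mean that the surplus power seen on the printed inputs may not exist. The reader cannot tell which.

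The paragraph also sets expectations about attrition. Under Missing data, a patient who misses one of the three treatment blocks is excluded, so the number of completers that still supports 90% power matters. The text suggests that it is 18; the printed inputs put it at about 10.

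**Working it through.** **Inputs** (Sample size calculation): SD 38; correlation 0.5; difference 57; two-sided alpha 0.0167; power 0.90. Design: three-treatment crossover (Regimen).

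**The plan's own figures**
- Difference: 0.35 × 164 = 57.4. The stated 57 is reproduced.
- Dropout: 1 − 18/22 = 18.2%. The step from 18 to 22 is consistent with a loss of about 18%.
- 18 patients: not reproduced, as follows.

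**SD of a within-patient difference**

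38 × √(2 × (1 − 0.5)) = 38, so the standardised difference is 57/38 = 1.5.

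**Normal approximation**

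n = (2.393 + 1.282)² / 1.5² = 6.0.

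**Noncentral t**, with noncentrality 1.5 × √n:

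| Degrees of freedom | n | Power for 57 |
|---|---|---|
| n − 1 (paired t) | 9 | 89.65% |
| n − 1 | 10 | 93.98% |
| n − 1 | 18 | 99.97% |
| 2n − 4 (three-treatment crossover) | 7 | 83.9% |
| 2n − 4 | 8 | 90.7% |

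The 2n − 4 comes from 3n observations, less 1 for the mean, n − 1 for patients, 2 for periods and 2 for treatments. So 10 patients are needed by paired t and 8 with crossover degrees of freedom.

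**Could a small change in the inputs close the gap?**
- Using 57.4 instead of 57: paired t gives 9.
- Correlation 0 instead of 0.5: SD of the difference 53.7, and paired t gives 16, still below 18.
- Solving paired t for n = 18 at exactly 90% power: SD of the difference = 60.1. With SD 38 this requires a correlation of 1 − 60.1²/(2 × 38²) = −0.25. With correlation 0.5, the SD of the AUC itself would have to be about 60.

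**What 18 patients can detect on the printed inputs**

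By paired t, 90% power is reached at a standardised difference of 0.948, and 0.948 × 38 = 36.0. That is 22% of 164, or 36/28 = 1.3 NPRS points per day over 28 days.

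**28 against 35 days**

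SD 38 belongs to a 28-day AUC, while the primary outcome is a 35-day AUC (Outcome measures). If the SD scales with duration, which is an assumption, it becomes 38 × 35/28 = 47.5. The difference detectable with 18 patients is then 0.948 × 47.5 = 45.0.

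**The case against.** The strongest reply is that the error is on the safe side. On the printed inputs, 18 patients exceed the promised 90% power for 57, and no endpoint, analysis or enrolment figure has to change. This stands, and it limits the severity.

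The surplus may also have a use. Under Statistical analysis, a significant sequence-by-treatment interaction restricts the analysis to the first period. With 18 to 22 patients that leaves about 6 or 7 per arm and, on the same SD and alpha, only 44% to 53% power for 57. The article does not give this as the reason for 18, so it does not explain the figure, but it is an argument against cutting the sample.

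The exact requirement depends on the method, which is why it is given as 8 to 10. The sentence is also garbled and cites a source that is not shown, so words or an input may be missing. That supports asking for the method; it does not make the printed statement correct.

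Three stronger readings are tempting and not supported:
- That the difference of 57 or the power claim fails. The 57 follows from 35% of 164, and the power is exceeded. What fails is the claim that 18 are needed.
- That the cause is known. The normal-approximation 6.0 times three treatments gives 18, but so do two parallel arms with the factor 1 − 0.5² = 0.75 (12.0 × 0.75 = 9.0 per arm, 18 in total). Neither fits a design in which every patient receives everything, and the article mentions neither.
- That the article presents 57 as the smallest effect a null result can exclude. It does not say so, and that question is answered by the confidence interval.

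**Conclusion.** The point holds as a reproducibility error of moderate severity. For the described crossover, the stated inputs call for about 8 to 10 patients, not 18, and rounding or the choice of degrees of freedom does not bridge the gap. Either the calculation does not match the design, or the SD or correlation printed is not the one used. The trial is not shown to be underpowered; that would become an open question only if the true SD of the within-patient difference were above about 60.

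The figures rest on three assumptions: the printed 38 is the between-patient SD of the AUC under each treatment, the correlation of 0.5 applies to any pair of periods, and there is no carryover, as the article assumes for sizing. All figures are on the 28-day scale unless stated.

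**What to change.** Keep 22 recruited and 18 completers. State the formula and the SD of the within-patient difference that were actually used, then correct whichever side is wrong.

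- If another SD or correlation was used, print it. For 18 to be the paired-t answer, the SD of the difference must be about 60.
- If SD 38 and correlation 0.5 stand, replace the claim with wording such as: about 10 completers reach 90% power at two-sided 1.67% for a 28-day AUC difference of 57, and 18 completers give 90% power for a 28-day AUC difference of about 36.
- Label these figures as 28-day, or rescale them to the 35-day primary endpoint. If the SD scales with duration, SD is about 47.5 and the difference detectable with 18 completers is about 45.

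The cost is one reworded paragraph, with no change to enrolment or analysis.
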